## Abstract

**Background:**

Stroke is a major public health threat globally. Psychosocial well-being may be affected following stroke. Depressive symptoms, anxiety, general psychological distress and social isolation are prevalent. Approximately one third report depressive symptoms and 20% report anxiety during the first months or years after the stroke. Psychosocial difficulties may impact significantly on long-term functioning and quality of life, reduce the effects of rehabilitation services and lead to higher mortality rates. The aim of the study is to evaluate the effect of a previously developed and feasibility tested dialogue-based psychosocial intervention aimed at promoting psychosocial well-being and coping following stroke among stroke survivors with and without aphasia.

**Methods:**

The study will be conducted as a multicenter, randomized, single blind controlled trial with one intervention and one control arm. It will include a total of 330 stroke survivors randomly allocated into either an intervention group (dialogue-based intervention to promote psychosocial well-being) or a control group (usual care). Participants in the intervention group will receive eight individual sessions of supported dialogues in their homes during the first six months following an acute stroke. The primary outcome measure will be psychosocial well-being measured by the General Health Questionnaire (GHQ). Secondary outcome measures will be quality of life (SAQoL), sense of coherence (SOC), and depression (Yale). Process evaluation will be conducted in a longitudinal mixed methods study by individual qualitative interviews with 15–20 participants in the intervention and control groups, focus group interviews with the intervention personnel and data collectors, and a comprehensive analysis of implementation fidelity.

**Discussion:**

The intervention described in this study protocol is based on thorough development and feasibility work, guided by the UK medical research council framework for developing and testing complex interventions. It combines classical effectiveness evaluation with a thorough process evaluation. The results from this study may inform the development of further trials aimed at promoting psychosocial well-being following stroke as well as inform the psychosocial follow up of stroke patients living at home.

**Trial registration:**

NCT02338869; registered 10/04/2014 (On-going trial).

## Background

Stroke is a major global health problem [1]. Psychosocial well-being is frequently threatened following stroke. Depressive symptoms, anxiety, general psychological distress and social isolation are prevalent [2]. Approximately one third report depressive symptoms and 20% report anxiety during the first months and depression may be present years after the stroke [3–5]. Psychosocial difficulties may impact significantly on long-term functioning and quality of life [4, 6], reduce the effects of rehabilitation services and lead to higher mortality rates [7].

A large number of studies have explored possible interventions to prevent and/or treat psychosocial problems [7–10], but results have generally been disappointing. Pharmacological treatment may be effective in treating post-stroke depression, but not in preventing it. Furthermore, antidepressants may have adverse effects in persons with stroke and should be used with care [7, 11]. Consequently, there is a need for developing alternative interventions. So far, psychosocial interventions have had modest effects; however, the findings conclude that information, emotional support, practical advice and motivational support are important [8, 10, 12, 13]. It remains unclear how the different elements of the interventions contribute to positive outcomes and which elements work best at different stages and among different subgroups [8, 10, 12]. Few studies have provided adequate theoretical accounts of the mechanisms assumed to contribute to positive outcomes [8, 10, 12].

Aphasia affects about one third of the stroke population [14] and 40% continues to have significant language impairment at 18 months post-stroke [15]. Language is the most important tool for human interplay, social participation and community. Aphasia is associated with major disruptions of everyday life and affects all dimensions of quality of life [16, 17]. Persons with aphasia (PWA) are especially prone to psychosocial problems, such as anxiety and depression, threatened identity, changes in interpersonal relationships, reduced social networks, social isolation, unemployment and abandonment of leisure activities [18–23]. The emotional and psychosocial factors have a marked impact on recovery, the psychosocial adjustment process, and the response to rehabilitation [24, 25]. Nevertheless, psychosocial interventions targeting this group are sparse and access to such services very limited.

The incidence of stroke increases dramatically with increasing age [1]. However, stroke may appear at any age. Among younger work-aged stroke survivors (aged 18–67 years), the psychosocial factors appear to have at least as great an impact on life after stroke as the physiological consequences [26–28]. Despite the potential serious consequences among younger persons, few intervention studies have sought to develop psychosocial interventions tailored to their specific needs.

Registered nurses (RNs) are among the members in the rehabilitation team who are expected to address the psychosocial needs of patients through providing support and guidance to improve coping [29, 30]. Nevertheless, only a few nursing interventions have been developed, specifically addressing the psychosocial well-being of stroke survivors [31–34]. These are promising, but have mostly been conducted by hospital-based staff. However, a major thrust of the rehabilitation occurs in the community. Consequently, effective interventions for primary health care are needed. Nurses are the most numerous professionals within this sector and are frequently the front line workers providing care to stroke survivors. Other health care professionals as well, including occupational therapists (OTs), are responsible for promoting coping and adjustment to the consequences of stroke [35, 36]. However, few interventions delivered by primary health care professionals have been developed and tested.

To address this void, we have developed and initially tested a dialogue-based psychosocial intervention primarily carried out in primary care, aimed at supporting the coping and life skills of stroke survivors [37]. In this work, we applied a development and testing approach consistent with the recommended framework for developing and evaluating complex interventions proposed by the UK Medical Research Council [38, 39]. This framework describes the development and testing of complex health interventions in four interacting phases, from the initial development phase, through the ‘modeling’ and ‘exploratory trial’ phases into the ‘RCT’ phase and finally the ‘long-term implementation’ phase. In our previous studies, we have completed the first three phases. In the first two phases, we reviewed relevant research and theory to develop an empirical- and theory-based intervention [37]. In the exploratory trial phase, we used a multiple case study approach, drawing on different data sources to explore if the intervention was found useful by twenty five stroke patients [40].

The participants in the exploratory trial/feasibility study found the content and process of the intervention relevant. The participants underscored the benefits of being supported through a difficult time, provided a chance to tell and (re)create their story and being supported in their attempts to cope with the situation. Receiving psychological support and motivation to move on during the difficult adjustment process, and exchange of knowledge and information were also experienced as beneficial and important by the participants [41–44]. The aphasia group emphasized the importance and experienced benefit of receiving language support through the opportunities to speak and being supported in communicating about their experiences by a knowledgeable dialogue partner [41, 42]. The study provided initial support for the usefulness of the psychosocial intervention and suggested aspects that needed further consideration and development. In particular, the intervention should be further developed for persons with aphasia. In addition, the younger participants (i.e. people in working-age) emphasized the need for a psychosocial program that specifically addressed their particular challenges and needs as carers for children, breadwinners in their families and as employees struggling to return to work [43]. Based on these findings, testing in a larger, controlled trial is warranted.

In the current study, we use the same content, structure and process that were tested in the initial exploratory trial/feasibility study. However, based on the findings from the preliminary work, we have adjusted the intervention to accommodate the weaknesses and challenges uncovered in the exploratory trial/feasibility study.

### Aims and hypotheses

The primary aim of the study is to determine whether a previously developed and feasibility-tested dialogue-based psychosocial intervention promotes psychosocial well-being and coping following stroke among stroke survivors with and without aphasia, compared to usual care. We will test the following hypotheses:*Primary outcome:* Stroke survivors with and without aphasia in the intervention group will experience significantly higher levels of psychosocial well-being and lower levels of depressive symptoms and anxiety (measured by GHQ-28) than stroke survivors in the control group at 6 and 12 months post stroke*Secondary outcomes:* Stroke survivors with and without aphasia in the intervention group will experience significantly higher levels of sense of coherence (measured by SOC-13) and health-related quality of life (measured by SAQOL-39) than stroke survivors in the control group at 6 and 12 months post stroke

The secondary aim of this study is to conduct a process evaluation in order to understand the change mechanisms of the intervention and how these impact on the participants’ study outcomes. To improve our ability to interpret the study outcomes, the process evaluation will assess:How participants in the intervention and control group experience their adjustment process following the stroke and their participation in the studyHow the personnel delivering the intervention experiences their role in the intervention delivery and the participants’ responsiveness to the interventionHow the data collectors experienced the data collection interviews with the participants, including the acceptability and/or difficulties in applying the instruments in this populationImplementation fidelity and intervention adherence throughout the study

## Methods

### Design

The study is a prospective multicenter randomized controlled trial to evaluate the effectiveness of a dialogue-based longitudinal intervention study the first six months following a cerebrovascular stroke for persons with and without aphasia. The trial has one intervention and one control arm. The process evaluation is a longitudinal mixed-methods study. The protocol is prepared according to the Standard Protocol Items: Recommendations for Interventional Trials (SPIRIT).

### Setting

The study is primarily conducted in community care settings in Norway. The intervention is mainly delivered in the homes of the participants. However, in the initial phases, the dialogue-based sessions may be conducted in other settings if necessary, such as in a hospital, at a rehabilitation unit or another place where the participants find themselves. The intervention is delivered by specially trained nurses and occupational therapists.

### Participants

#### Inclusion and exclusion criteria

This RCT study includes stroke survivors meeting the following inclusion criteria: Being adults over 18 years of age, suffered an acute stroke within the last month prior to inclusion, medically stable, sufficient cognitive functioning to participate (assessed by their physician/stroke team), interested in participating, able to understand and speak Norwegian, and able to give informed consent.

Exclusion criteria include moderate to severe dementia, serious somatic or psychiatric disease as these are assumed to impact on the ability to participate in the intervention. All participants are screened for aphasia using the Ullevaal Aphasia Screening Test (UAS) [41], and a speech therapist will be consulted if needed. Persons will be excluded if they have significant impressive aphasia or severe expressive aphasia, but will otherwise be included.

### Sample size calculations

The study’s sample size was calculated based on the primary outcome measure GHQ-28, which has been used in a comparable trial [31, 32]. Following Watkins et al.’s results, we deemed an odds ratio of 1.6 or higher between-groups (intervention/control) with normal mood after 6 and 12 months to be clinically relevant. The calculations are based on a repeated measures logistic regression model for the output variable “normal mood” (GHQ-28 < 5) with two measurements for each patient (i.e. one at 6 months and one at 12 months), with one binary input variable specifying group allocation. Based on 80% power across both time points, the calculated sample size of this study is 300 participants, 150 in each arm of the study. To allow for a 10% dropout rate, we have inflated the number to 330 participants in total.

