### Statistical analysis

Data analysis will be conducted as intention-to-treat. Missing data will be imputed using multiple imputation technique [71]. All analyses will be performed using statistical software such as IBM SPSS or R. For group comparisons of individual variables, categorical variables will be analyzed using chi-squared tests, and continuous variables will be analyzed using t-tests or Mann-Whitney U tests (for two-group comparisons) and F-tests or Kruskal-Wallis tests (for more than 2 groups). The primary statistical analysis will be a repeated measures logistic regression model for the dichotomized output variable “normal mood yes/no” (GHQ-28 < 5 versus GHQ-28 ≥ 5) with two measurements for each patient (i.e. one at 6 months and one at 12 months), with one binary input variable specifying group allocation. Independent variables will include demographic variables, stroke type and severity measurements, rehabilitation service use and relevant medical variables. Medical and demographic variables will be included in the data analysis model to control for group differences at baseline. Secondary analyses, e.g. sub-group analyses, will be conducted with primary, secondary and process outcomes. The psychometric properties of GHQ-28 will be examined to confirm stability of dimensions in a Norwegian general stroke population across time points. All statistical tests will be performed as two-sided tests with a significance level of 0.05.

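### 150 per arm gives 80% power for an odds ratio of 1.6 only if a patient's 6- and 12-month results are essentially uncorrelated; at correlations of 0.3 to 0.5 power is about 60 to 71%

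*Protocol article*

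**What the plan says.** All references are to the protocol article.

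- **Effect size** (Sample size calculations): "we deemed an odds ratio of 1.6 or higher between-groups (intervention/control) with normal mood after 6 and 12 months to be clinically relevant".
- **Model** (same section): "The calculations are based on a repeated measures logistic regression model for the output variable" normal mood, defined as GHQ-28 below 5, "with two measurements for each patient (i.e. one at 6 months and one at 12 months), with one binary input variable specifying group allocation".
- **Result** (same section): "Based on 80% power across both time points, the calculated sample size of this study is 300 participants, 150 in each arm".
- **Dropout** (same section): "To allow for a 10% dropout rate, we have inflated the number to 330 participants in total".
- **Test level** (Statistical analysis): "All statistical tests will be performed as two-sided tests with a significance level of 0.05". That section also names the same repeated-measures logistic model as the primary analysis.

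The article gives neither the control-group proportion with normal mood nor the correlation between a patient's 6- and 12-month results.

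**The concern.** Two binary results from one patient six months apart carry less information than results from two different patients. How much less depends on their correlation. The printed sample size is about half of what one measurement per patient would require, which is the answer obtained when the two results are treated as independent. That is hard to reconcile with a calculation described as repeated measures.

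At stake is the main design claim. The article calls an odds ratio of 1.6 clinically relevant and says the trial has 80% power for it. If the true power is nearer two thirds, a reader of a null primary result who relies on the 80% will take it as stronger evidence against a relevant effect than it is.

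**Working it through.** **Inputs from the article.** Odds ratio 1.6; 80% power; 150 per arm, 1:1; two measurements per patient; group as the only covariate in the sample size model; two-sided 0.05 (Statistical analysis).

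**Inputs assumed, because the article does not give them.** Control-group proportion with normal mood p0, taken as 0.30 to 0.60 and equal at both visits. Within-patient correlation rho, taken as 0 to 0.7. The odds ratio is read as marginal and equal at both visits.

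**Step 1: one measurement per patient.**

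n per arm = (z_0.975 + z_0.80)² × [1/(p0·q0) + 1/(p1·q1)] / (ln 1.6)², where p1 = 1.6·p0/(1 − p0 + 1.6·p0), q0 = 1 − p0 and q1 = 1 − p1.

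At p0 = 0.50, p1 = 0.8/1.3 = 0.615. The bracket is 4.000 + 4.225 = 8.225. Then n = (1.960 + 0.8416)² × 8.225/0.470² = 7.849 × 8.225/0.2209 = 292 per arm.

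**Step 2: two measurements per patient.** Multiply by (1 + rho)/2. At rho = 0 and p0 = 0.50 this is 292/2 = 146. For p0 from 0.35 to 0.55 the rho = 0 requirement runs from 145 to 152, so the printed 150 is reproduced under independence.

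**Step 3: the largest rho that still gives 80% with 150 per arm.** Set n × (1 + rho)/2 = 150, so rho = 300/n − 1.

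| p0 | n per arm, one measurement | largest rho for 80% |
|---|---|---|
| 0.30 | 316 | −0.05 |
| 0.35 | 299 | 0.00 |
| 0.40 | 290 | 0.03 |
| 0.45 | 288 | 0.04 |
| 0.50 | 292 | 0.03 |
| 0.55 | 302 | −0.01 |
| 0.60 | 319 | −0.06 |

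The maximum is about 0.04, near p0 = 0.45 (about 0.05 with a pooled score test). At p0 of 0.30 or 0.60 power is about 78% even at rho = 0.

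**Step 4: power with 150 per arm.** Power = Φ( ln 1.6/SE − 1.96 ), with SE² = [1/(p0·q0) + 1/(p1·q1)] × (1 + rho)/(2 × 150).

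| rho | power at p0 = 0.50 | power over p0 = 0.30 to 0.60 |
|---|---|---|
| 0 | 81% | 78–82% |
| 0.1 | 77% | 74–78% |
| 0.2 | 74% | 70–74% |
| 0.3 | 70% | 66–71% |
| 0.5 | 64% | 60–65% |
| 0.7 | 59% | 55–59% |

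A simulation of marginal logistic regression with robust variance (20,000 runs per setting, p0 = 0.40) gave 81.9%, 71.3%, 64.3% and 59.4% at rho 0, 0.3, 0.5 and 0.7, in agreement with the formula.

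**Step 5: what 80% power would need.** Over p0 = 0.30 to 0.60, the requirement is about 188–208 per arm at rho 0.3, 217–240 at rho 0.5 and 246–272 at rho 0.7. Equivalently, at rho 0.5 and p0 of 0.40 to 0.60, 150 per arm has 80% power for an odds ratio of about 1.76 to 1.83.

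**Dropout.** 300 × 1.10 = 330, but 330 × 0.90 = 297; retaining 300 after 10% loss needs 300/0.90 = 334. The effect on power is under one percentage point.

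**The case against.** The strongest reply is that the replacement power rests on a correlation the article does not give. Nothing in it identifies 0.3 to 0.5 as the right range, and at rho 0.1 power would still be 74 to 78%. This stands as a caution: no single figure should replace the 80%. It does not save the 80%, because the bound of about 0.04 to 0.05 holds at the most favourable control rate.

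A second reply is that the article is condensed, and that the treatment of the two results as independent is inferred by working backwards. The printing of the inputs can indeed be left to the full protocol. But with the odds ratio, test level, model and sample size all given, no choice of control rate yields 80% without near-zero correlation. A one-sided 5% calculation would give about 80% at rho 0.2 to 0.3. If that was done, the planning contradicts the two-sided test in Statistical analysis, and the two-sided shortfall remains.

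Third, all 330 patients might be retained or imputed. With 165 per arm and no loss, power is 71 to 75% at rho 0.3 and 64 to 68% at rho 0.5, still short of 80%. The planned covariates could change power somewhat, but the stated calculation uses group alone, so they cannot justify its result.

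Finally, randomisation, type I error and the estimate are unaffected, and the confidence interval shows what a null result excludes. That is correct. It limits the harm to the design claim and to how a null result is read.

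**Conclusion.** The concern holds. At two-sided 5%, 150 per arm and a marginal odds ratio of 1.6 give 80% power only if the 6- and 12-month results within a patient are essentially uncorrelated. That is implausible for the same questionnaire in the same patients, and the primary hypothesis itself expects the benefit at both times.

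For control rates of 30 to 60%, power is about 66 to 71% at rho 0.3 and 60 to 65% at rho 0.5. The chance of missing an odds ratio of 1.6 is therefore about 29 to 40% over that range of rho, against the stated 20%. Both rho and the control rate are assumptions, but the finding that power is below 80% at any appreciable positive correlation does not depend on which values are chosen. If 1.6 was meant as a subject-specific odds ratio from a random-intercept model, the marginal effect is smaller and power is lower still.

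**What to change.** Enrolment should not be reopened: the Trial status section says recruitment has ended. Correct the sample size statement in the analysis plan and in the results paper:

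1. State the control-group rate, the within-patient correlation and the sidedness used in the calculation, and whether 1.6 is a marginal or a subject-specific odds ratio.
2. Replace the single 80% with power over a range of correlations. For example, 300 evaluable patients at a 50% control rate give 70%, 64% and 59% power at rho 0.3, 0.5 and 0.7; or, at rho 0.5, 80% power for an odds ratio of about 1.8. Label these values of rho as assumptions.
3. State that a non-significant primary result does not by itself exclude an odds ratio of 1.6, and interpret it from the confidence interval.
4. As a minor correction, give 297 as the number expected after 10% loss from 330.

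The cost is a rewritten paragraph and a less favourable stated power. No data collection or analysis changes.

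### The 10% dropout allowance is added to 300 rather than divided out, so 330 enrolled covers about 9.1% dropout and leaves 297 completers at 10%; the effect on power is minor

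*Protocol article*

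**What the plan says.** The Sample size calculations section of the protocol article takes an odds ratio of 1.6 for normal mood (GHQ-28 below 5) and a repeated measures logistic model with outcomes at 6 and 12 months. It continues: "Based on 80% power across both time points", "the calculated sample size of this study is 300 participants, 150 in each arm of the study". The allowance for loss follows: "To allow for a 10% dropout rate, we have inflated the number to 330 participants in total". No inflation formula is given. The Methods paragraph of the abstract repeats the enrolment figure: "It will include a total of 330 stroke survivors".

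Three other places bear on the point:

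- **Statistical analysis** plans an intention-to-treat analysis with multiple imputation of missing data, and sets the test level: "All statistical tests will be performed as two-sided tests with a significance level of 0.05".
- **Process evaluation** expects attrition to differ between the arms.
- **Trial status** reports that recruitment to the trial has closed.

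**The concern.** The section gives three linked numbers: 300 required, 10% dropout, 330 enrolled. They do not fit together. Dropout is a fraction of the people who enter the trial, so the number to enrol is the number required divided by the fraction retained. Adding 10% of the smaller number gives too few. At the plan's own dropout rate, the plan's own enrolment falls below the 300 on which its 80% power rests.

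What is at stake is the accuracy of a reported design figure. The slip is separate from whether 300 is the right base. If the base were revised and again multiplied by 1.10, the result would again fall 1% short, because 1.10 × 0.90 = 0.99.

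**Working it through.** **Inputs from the document.** Required number 300 (150 per arm), dropout 10%, enrolment 330, power 80% (all from Sample size calculations); two-sided 0.05 (Statistical analysis).

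**Step 1: reproduce the plan's figure.**
300 × (1 + 0.10) = 330. This matches exactly, so the allowance was evidently added rather than divided out.

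**Step 2: apply the stated dropout to the stated enrolment.**
330 × (1 − 0.10) = 297, or 165 × 0.90 = 148.5 per arm against 150. The shortfall is 3 of 300, or 1.0%.

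**Step 3: enrolment that would keep 300.**
300 / (1 − 0.10) = 333.3, rounded up to 334 (167 per arm; 167 × 0.90 = 150.3). That is 4 more than 330, and 4/330 = 1.2%.

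**Step 4: dropout that 330 does cover.**
(330 − 300) / 330 = 30/330 = 9.1%.

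**Step 5: effect on power, taking 300 as giving exactly 80%.**
Power(N) = Φ[(z₀.₉₇₅ + z₀.₈₀) × √(N/300) − z₀.₉₇₅], with z₀.₉₇₅ = 1.960 and z₀.₈₀ = 0.842.

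- N = 297: 2.802 × √0.99 = 2.788; 2.788 − 1.960 = 0.828; Φ(0.828) = 79.6%.
- N = 300: 80.0% by construction.
- N = 330, if no information were lost: 83.6%.

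The loss from 300 to 297 is 0.4 percentage points.

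**Step 6: does that loss depend on taking 300 as exactly 80%?**
The document gives neither the control-arm rate of normal mood nor the correlation between the two visits, so both are assumed here. The variance of the log odds ratio is (1 + ρ)/2 × [1/(n p(1 − p)) + 1/(n q(1 − q))], with n = N/2 per arm, p the control rate, and q the rate implied by an odds ratio of 1.6.

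| Assumed control rate | Assumed ρ | Power at 300 | Power at 297 |
|---|---|---|---|
| 0.3 | 0 | 77.9% | 77.5% |
| 0.4 | 0 | 81.3% | 80.9% |
| 0.5 | 0 | 81.0% | 80.6% |
| 0.6 | 0 | 77.5% | 77.1% |
| 0.5 | 0.5 | 64.0% | 63.5% |

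The level of power moves a great deal with these assumptions. The cost of the dropout step stays at about 0.4 points throughout.

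**The case against.** The strongest case against raising this is that it changes nothing. Adding the percentage is a common shortcut, the 10% is a round planning guess, and 9.1% is close to it. The base of 300 is itself uncertain by more than 3 people: with uncorrelated visits and assumed control rates of 0.3 to 0.6, the required total runs from about 290 to 319. Enrolment is closed, and observed attrition will replace the guess. All of this stands, and it is why the point is minor. It does not make 297 equal 300, and nothing else in the article reconciles the three numbers.

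A second objection is that dropouts are not simply discarded. This also stands in part. The primary model uses two visits, so a person lost after 6 months supplies one observed outcome, and multiple imputation keeps all randomized participants in the analysis. Imputation does not in general restore the information of an observed outcome, but calling the 297 the only evaluable participants would be too strong. They are the participants with both follow-ups.

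A third is that the 10% may have meant 10% of 300. That would explain the 330, but it is not a dropout rate among those enrolled, and the sentence would need to say so.

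A reader might infer from the gap that the trial is underpowered. The document does not support that. The gap costs at most about 0.4 points, and in two of the uncorrelated scenarios above 297 still exceeds 80%. Where power is well below 80%, the cause is the assumed correlation acting on the base of 300, not the dropout step.

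**Conclusion.** The point holds as a small arithmetic slip. At the stated 10% dropout, 330 enrolled leaves 297 with complete follow-up, not 300. The gap is 3 completers (1.0%) or 4 enrolled (1.2%), and 330 covers about 9.1% dropout.

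The power cost is about 0.4 percentage points, for example 80.0% to 79.6%. This rests on two assumptions: that 300 gives exactly 80%, and that dropouts contribute nothing. The second makes it an upper bound, since 6-month outcomes and imputation recover some information; on the same base, power lies between 79.6% and the 83.6% that 330 participants without loss would give. The calculation also takes losses as equal across the arms. The differential attrition expected under Process evaluation would put one arm below 148.5, but would add little to the power loss at 10% overall.

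This finding neither confirms nor refutes the base figure of 300.

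**What to change.** Because recruitment has ended, correct the wording and leave enrolment alone. Replace the dropout sentence in Sample size calculations with one of these:

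- 330 enrolled allows for about 9% dropout; or
- 330 enrolled with 10% dropout leaves 297 participants with complete follow-up.

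If power is restated anywhere, use 297 completers, and note that participants seen only at 6 months and the planned imputation add some information beyond that count.

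The cost is one sentence. The reported figure becomes slightly less favourable; the analysis and the conduct of the trial do not change, and no further participants are needed.
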